|------------|------------|-------------------------------------------------------------------------------------------------------------------------------------------------------------------------------------------------------------------------------------------------------------------------------------------------------------------------------------------------------------------------------------------------------------------------------------------------------------------------------------------------------------------------------------------------------------------------------------------------------------------------------------------------------------------------------------------------------------------------------------------------------------------------------------------------------------------------------------------------------------------------------------------------------------------------------------------------------------------------------------------------------------------------------------------------------------------------------------------------------------------------------------------------------------------------------------------------------------------------------------------------------------------------------------------------------------------------------------------------------------------------------------------------------------------------------------------------------------------------------------------------------------------------------------------------------------------------------------------------------------------------------------------------------------------------------------------------------------------------------------------------------------------------------------------------------------------------------------------------------------------------------------------------------------------------------------------------------------------------------------------------------------------------------------------------------------------------------------------------------------------------------------------------------------------------------------------------------------------------------------------------------------------------------------------------------------------------------------------------------------------------------------------------------------------------------------------------------------|
| 08-10-2024 | 11-10-2024 | 
1. Sub-study: During the course of data analysis, the primary outcome of 'major adverse cardiovascular events' trended to benefit (although not statistically significant) and 'unplanned all-cause hospitalization/emergency department (ED) visit' saw a statistically significant reduction of 28% (<math>p = 0.01</math>). To further explore this finding, long term care facility residents will be observed for an additional 1 year post planned final analysis with a repeat analysis of all outcomes conducted in March of 2025. Several months after the end of data collection we reached out to all participating facilities and were told that none of the participants' antihypertensive medication timings had been changed. We would like to ask them to continue with those allocations, given we have demonstrated no harm and the possibility of benefit for bedtime prescribing which requires further exploration.
 
2. Chronotype category analysis: Given a recent antihypertensive timing trial (TIME) demonstrated that chronotype, which is defined by the time of day people are most active (often referred to as early birds or night owls), might influence the effect of antihypertensive timing on cardiovascular events, we would like to explore this with the BedMed-Frail data as well. Although chronotype itself is not available in the RAI-MDS data, there are three things which we feel may create a rough approximation for chronotype. These are the description of the time of day when patients are active (morning, midday, evening), problems with insomnia, and use of sleeping pills. We would define early birds as being those who are active in the morning and not the evening and we would define night owls as being those who are active in the evening but not the morning or those who have insomnia or are using sleeping pills. We would like to repeat the analysis of the primary outcome and the analysis of all cause unplanned hospitalization/ED visits using early bird and night owl as covariates in the survival analysis carried out for each of these outcomes, as well as including an interaction term between allocation and each of these chronotype covariates. In so doing, we would be looking to see if the hazard ratio and p-value for those covariates suggests an influence of chronotype on the effects of medication timing on mortality and morbidity.
 |
|------------|------------|-------------------------------------------------------------------------------------------------------------------------------------------------------------------------------------------------------------------------------------------------------------------------------------------------------------------------------------------------------------------------------------------------------------------------------------------------------------------------------------------------------------------------------------------------------------------------------------------------------------------------------------------------------------------------------------------------------------------------------------------------------------------------------------------------------------------------------------------------------------------------------------------------------------------------------------------------------------------------------------------------------------------------------------------------------------------------------------------------------------------------------------------------------------------------------------------------------------------------------------------------------------------------------------------------------------------------------------------------------------------------------------------------------------------------------------------------------------------------------------------------------------------------------------------------------------------------------------------------------------------------------------------------------------------------------------------------------------------------------------------------------------------------------------------------------------------------------------------------------------------------------------------------------------------------------------------------------------------------------------------------------------------------------------------------------------------------------------------------------------------------------------------------------------------------------------------------------------------------------------------------------------------------------------------------------------------------------------------------------------------------------------------------------------------------------------------------------------|

# BedMed-Frail Statistical Analysis Plan

## **Adaptive Randomization (conversion to modified intention-to-treat)**

Participating facilities are volunteering to support our trial with no financial compensation, and “fitting it in” with other work. For several facilities, COVID-19, other infectious outbreaks, and implementation of other facility initiatives has led to long delays before the facility pharmacist was able to act on their allocation list. For a few facilities this delayed implementation by several months. Given 1) we are placing an equal emphasis on detecting harm, 2) long implementation delays make both groups look more similar and reduce the ability to detect harm, and 3) no action of any kind was taken related to the facility’s allocation list in this interval, we have adapted the trial to consider the date of each facility’s initial randomization to be the date the allocation list was actually acted upon, and not the date it was generated. This date was determined by the AHS data analyst, using electronic pharmacy dispensing data, to be the day before the first switch of an eligible patient’s BP medications from morning to bedtime. Individuals who, on the date of implementation, were no longer resident in the facility, hospitalized, or without once daily BP meds, were excluded from the trial.

## **Outcomes**

Unless otherwise stated, all outcomes are recorded over the duration of the study.

### *Primary:*

Major adverse cardiovascular events (MACE)

- Defined as first occurrence of either all-cause death or hospital admission / emergency department (ED) visit for acute coronary syndrome / myocardial infarction (MI), stroke, or congestive heart failure (CHF)

### *Secondary Efficacy:*

1. Each component of the primary outcome individually.
2. All-cause unplanned hospitalization / ED visit (per Canadian Institute for Health Information DAD Abstracting Manual’s definition of “urgent/emergent” – which excludes elective surgeries or booked procedures / planned follow-up care)

### *Secondary Safety:*

1. Non-vertebral fracture
2. Fall in the last 30 days\*
3. Urinary incontinence ( $\geq$  “occasionally incontinent” = 2 or more times per week)\*
4. Partial or full thickness decubitus skin ulceration (i.e. stages 2 to 4)\*

### *Cognitive / Behavioral*

5. “Deteriorated cognition relative to status 90 days prior”\*
6. “Behavioral symptoms that are present a minimum of 4 days per week and not easily altered in the last 7 days” (includes wandering, verbal abuse, physical abuse, socially inappropriate or disruptive behavior, and resisting care)\*

7. Receipt of antipsychotic medication or physical restraints (chair, trunk, or limb restraints, does not include bedrails) in the last 7 days\*
8. Receipt of anti-anxiety medication on  $\geq 3$  of the last 7 days\*
9. Receipt of a bedtime sleeping pill on  $\geq 3$  of the last 7 days\*
10. “Indicators of depression or anxiety almost daily” in the last 30 days (applies to 16 discrete mood and anxiety related observations of the resident, any one of which being listed as present 6 or more days per week would qualify)\*

\* Safety outcomes 2 – 10 will only be examined in LTC residents (and not Level 4 or 4D residents), as these measures are not as regularly collected on those who reside in facilities with a lower level of care. Each are binary outcomes as recorded by usual care nurses in the Quarterly RAI-MDS report in the 3- to 6-month window post-randomization (on average these assessments should take place roughly 135 days post-randomization, and the assessment closest to 135 days is chosen when more than one is available)

#### *Cost:*

1. Acute care costs (estimated from each hospital / ED admission’s resource intensity weight and length of stay)
2. Total cost of care (acute care costs + medication costs + physician billings + nursing / facility costs; with nursing / facility costs being estimated from level of care and duration of stay).

#### *Process:*

1. Proportion of BP medication doses taken at bedtime post-randomization, broken down on a monthly basis (with medications dosed more than once a day being considered as  $\frac{1}{2}$  dose in the AM and  $\frac{1}{2}$  dose in the PM for this calculation).
2. Use of at least one once-daily BP medication at Bedtime.
  - Note: Both of these process outcomes are determined, for each facility and for the study as a whole, using the “directions for use” field in Pharmaceutical Information Network (PIN) data. Each will be presented as a monthly time series, and will use only those randomized participants who are alive and resident at that facility at the end of each respective month.

## **Statistical Analysis**

### **Intension-to-treat assumptions**

*Loss to follow-up:* If participants change continuing care facilities within Alberta, we will no longer be able to control their medication timing, which is likely to default to morning use upon entering a new facility. As such, we will censor residents who change facilities on the first day of residence in the new continuing care facility. However, we will not censor patients transferred to “inpatient LTC” at a local hospital, as that is likely to represent an escalation in care due to acute illness, or diminished capacity. If such individuals improve, they may return to the original continuing care facility and we can continue to follow them. If not, the transfer to “inpatient LTC” likely signals a

deterioration of health that may precede adverse health outcomes that would be important to capture. If residents change their level of care, but remain in the same facility (i.e. move to a different floor, or wing, which has a different level of care), we will continue to follow them, as their medication timing is unlikely to change.

*Withdrawal:* Residents who do not want to participate in BedMed-Frail are generally “opted out” (i.e. excluded) prior to randomization. Should we be approached, by a resident, their family, or their providers, to opt-out a resident after randomization, that is likely to be prompted by an attempted timing change, and hence a more likely occurrence for those allocated to bedtime. To avoid the introduction of attrition bias, all post-randomization opt-outs will be included and analyzed per their allocation unless we are explicitly asked not to follow their electronic health data.

*Missing MDS data:* For each analysis, we will use the post-randomization MDS nursing report closest to day 135 (tie going to the later date). If there are no such post-randomization reports we will use the report immediately preceding randomization. If no reports of any kind are available (which should not occur as a baseline MDS report is a routine part of every admission), we will exclude the participant from the analysis.

*Nonadherence:* Nonadherence to allocation will not exclude participants from any of our planned analyses. However, as outlined in Sensitivity Analysis below, we will conduct a per-protocol analysis to determine whether results differ when adherence to allocation is highest.

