## **RESEARCH METHOD/PROCEDURES:**

**A) SETTING:** Alberta is home to the Institute for Continuing Care Education and Research (ICCER), a network of long-term care facilities intent on providing new knowledge relevant to improving quality of care for their residents. Working with their Executive Director ([name]) the BedMed investigators have approached, and obtained, support for BedMed-Frail from multiple ICCER-affiliated LTC organizations. Currently this includes the Bethany Care Society, Capital Care, Shepherd's Care, Sherwood Care, Wingkei, and Lifestyle Options Retirement Communities. Other facilities might join in before randomization begins. Collectively these facilities would have approximately 1200 eligible residents during the 2-3 year study period.

**B) DATA SOURCE:** All our outcomes and baseline covariates are derived from routinely collected electronic health data. This includes Ministry of Health / Health Authority administrative claims data (physician billings, vital statistics, emergency and hospital separations, prescriptions dispensed) and quarterly clinical care data captured by all LTC facilities in the Minimum Data Set (MDS) which is recorded quarterly in all institutions for all residents. To access and analyse this data (both administrative claims and MDS) we are partnering with the Alberta SPOR Data Platform through [name] (*Senior Biostatistician, Patient Health Outcomes and Clinical Effectiveness Unit, Alberta Health Services*) and his team of AHS biostatisticians.

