### Sensitivity Analyses

- 1) We will conduct a per-protocol analysis by excluding residents from any facility where fewer than 60% of medication doses are taken at bedtime in the intervention group 6-months post implementation.
- 2) We will conduct a full intention-to-treat analysis by including everyone who was initially assigned an allocation, even if they became ineligible (e.g., died) while waiting for their facility to act on the allocation list.

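### Follow-up stops when a resident moves to another continuing care facility, for an adherence reason, and the SAP's full intention-to-treat sensitivity analysis does not lift that censoring

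*Combined protocol and SAP*

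**What the plan says.** The rule is in the SAP's section on intention-to-treat assumptions, under Loss to follow-up: "As such, we will censor residents who change facilities on the first day of residence in the new continuing care facility". It applies to moves between continuing care facilities within Alberta. The justification is that "we will no longer be able to control their medication timing, which is likely to default to morning use upon entering a new facility".

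The same section keeps four other groups in follow-up:

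- residents transferred to inpatient LTC at a hospital, since the transfer may signal a "deterioration of health that may precede adverse health outcomes that would be important to capture";
- residents whose level of care changes within the same facility;
- residents opted out after randomization, analysed as allocated to avoid attrition bias, unless the team is explicitly asked not to follow their electronic data;
- nonadherent residents, who are excluded from none of the planned analyses.

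On data, the Protocol (Data Source) says: "All our outcomes and baseline covariates are derived from routinely collected electronic health data". It lists vital statistics and emergency and hospital separations among the sources. The primary outcome is the "first occurrence of either all-cause death or hospital admission / emergency department (ED) visit" for the named cardiovascular causes, and the SAP's Outcomes section adds: "Unless otherwise stated, all outcomes are recorded over the duration of the study".

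Under Sensitivity Analyses, item 2 reads: "We will conduct a full intention-to-treat analysis by including everyone who was initially assigned an allocation". It goes on to cover people who became ineligible while their facility had yet to act on the allocation list. It does not mention residents who move later.

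**The concern.** Expected reversion to morning dosing after a move is nonadherence. Elsewhere in the section nonadherence does not end follow-up; here it does, under an intention-to-treat heading and although the outcome can still be observed. The treatment of health-related moves is also uneven. A change in care level is followed if the new level is on the same site and censored if it requires another facility.

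Two things are at stake. First, the primary hazard ratio describes the effect while residents remain in their facility, whereas its label suggests the effect of allocation whatever happens later. Second, Cox regression assumes that censoring is unrelated to prognosis, given the covariates in the model. If allocation affected who moves, and movers were at higher risk, the two arms would lose high-risk residents at different rates. The plan neither reports moves by arm nor includes an analysis in which they would not matter.

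**Working it through.** **1. Does any planned time-to-event analysis follow residents past a move?**

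| Analysis | What it changes | Lifts the transfer censoring? |
|---|---|---|
| Primary | Counts from implementation; drops people ineligible by then | No, the rule applies |
| Sensitivity 1 (per-protocol) | Drops facilities with under 60% of doses at bedtime | Not stated |
| Sensitivity 2 (full intention-to-treat) | Restores everyone allocated | Not stated |

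Sensitivity analysis 2 changes who is included, not how long they are followed.

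**2. When would the censoring bias the hazard ratio?** The documents give no move rates, so every input here is assumed. Residents have an event hazard of 0.2/year, rising to 0.8/year on deterioration, with 2 years of follow-up and a true hazard ratio of 1. A given share of deteriorating residents (control vs bedtime) moves at the moment of deterioration. There were 2,000,000 simulated residents per scenario (Monte Carlo standard error about 0.002).

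| Deterioration rate per year | Censored HR, 30% vs 45% move | Censored HR, 10% vs 30% move | Censored HR, 30% in both arms |
|---|---|---|---|
| 0.1 | 0.975 | 0.967 | 1.00 |
| 0.2 | 0.957 | 0.955 | 1.00 |
| 0.3 | 0.945 | 0.938 | 1.00 |
| 0.5 | 0.939 | 0.933 | 1.00 |

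Without censoring the hazard ratio is 1.00 throughout. At a deterioration rate of 0.2/year with 30% vs 45% moving, a lag of 3 to 6 months before the move shrinks the bias to about 0.975 to 0.986.

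For scale, the standard error of the log hazard ratio at 301 events is 2/√301 = 0.115. A hazard ratio of 0.97 is |ln 0.97|/0.115 = 0.3 standard errors from 1, and 0.93 is 0.6.

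**3. Do the two analyses estimate the same thing?** Assume gamma frailty (mean 1, variance 0.5), a 3-year median at mean frailty, 2.5 years of follow-up, moves at 10%/year in both arms (at mean frailty), and an on-treatment hazard ratio of 0.724 that becomes 1 after a move. The censored analysis then gives about 0.74 and the uncensored one about 0.77 to 0.79. They are different quantities.

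**4. What would counting post-move events in the primary analysis cost in power?** First the plan's own figure: the Protocol gives 80% power at p = 0.05 for a 27.6% difference (HR 0.724) and stops at 301 events. With two-sided testing (assumed; not stated) and 1:1 allocation, events = 4(1.960 + 0.842)²/(ln 0.724)² = 31.40/0.1043 = 301, which agrees.

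Now let f be the share of events that follow a move, with no effect after it. Then ln HR = (1 − f) × ln 0.724, and power = Φ(½√301 × |ln HR| − 1.960).

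| f (assumed) | Average HR | Power at 301 events | Events for 80% power |
|---|---|---|---|
| 0 | 0.724 | 80% | 301 |
| 5% | 0.736 | 76% | 334 |
| 10% | 0.748 | 71% | 372 |
| 15% | 0.760 | 66% | 417 |
| 20% | 0.772 | 61% | 471 |

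The Protocol says events were inflated for noncompliance, yet 301 is the figure without inflation. If 27.6% already allows for some reversion, these losses are overstated.

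**The case against.** The strongest defence is that the rule was set in advance with a stated reason and targets a legitimate quantity, the effect while the resident is where timing can be managed. The SAP's adaptive randomization section puts equal emphasis on detecting harm and objects to anything that makes the arms look alike. Following movers through reversion to morning dosing would do that, and step 4 shows the cost could be substantial. This stands, and it is why replacing the primary analysis is not required.

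The two exceptions, inpatient LTC and same-site care-level changes, also keep two routes by which declining residents move. The remaining moves may be fewer and less related to health. This stands too.

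Falls, incontinence and behavioural symptoms are compared by arm, which is some check on reasons for moving. It is only partial, because these outcomes are limited to LTC residents and to one assessment, normally 3 to 6 months after randomization.

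A reader might infer that events are lost to the trial. The documents do not support that: the trial runs until 301 primary outcomes, so earlier censoring lengthens follow-up and leaves the planned event count unchanged.

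Finally, the sponsor may intend sensitivity analysis 2 to lift the censoring. The text does not say so, and one sentence would settle it.

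**Conclusion.** The point holds as a gap between label and analysis. The censoring rests on adherence, the outcomes remain observable, and as written no time-to-event analysis is full intention-to-treat. This follows from the text and needs no assumed figures.

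A reader might go further and conclude that the censoring is informative and the primary hazard ratio biased. The documents do not support that. They give neither rates of nor reasons for moves, and nothing in them shows that bedtime dosing changes who moves. With no true effect, moves must depend on both allocation and risk before bias arises. Under the assumptions in step 2 it takes the hazard ratio to about 0.97 to 0.93, towards apparent benefit when more bedtime residents move. With equal moves it is 1.00.

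Nor does the point reach every analysis in the plan: how the rule affects the MDS and cost outcomes is not described. It should be corrected, at low cost, because otherwise a reader of the results could not tell whether moves mattered.

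**What to change.** 1. Amend sensitivity analysis 2 so that every allocated resident is followed in provincial data through any change of facility until the event, departure from Alberta or study end. Keep the existing exception for anyone who asks that their data not be followed.
2. Report the number and timing of moves by arm.
3. Describe the transfer-censored primary analysis as the effect while resident in the facility, and do not call it intention-to-treat without that qualification.

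The cost is a few lines of SAP text, a tabulation and one further model run on data already linked. The sensitivity estimate will be diluted by residents who revert to morning dosing, and should be read that way. Making the uncensored analysis primary is optional and should be weighed against the power figures in step 4 once the share of events after a move is known.

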#### **D) Power/Sample Size Estimate:**

Expected Recruitment: At the time of this application we are collaborating with multiple ICCER-affiliated LTC organizations that wish to participate in this initiative. Most of these organizations have multiple facilities, many of which have multiple buildings or wings. Using Canadian Primary Care Sentinel Surveillance (CPCSSN) EMR data (accessed for the purpose of this application) we know that 53% of Canadians 80 yrs and older are listed as currently taking daily BP lowering medication. In our experience most of these medications are maintained upon nursing home admission. This suggests, given the 18-month median lifespan of newly admitted patients (and 9 month median lifespan of those already resident at the time of the study), that we should easily obtain 1200 residents total over the roughly 2-3-year duration of the trial.

Power: Utilizing well described methods for sample size determination, inflating the number of events to account for noncompliance, conservatively setting the median lifespan at 3 years to account for the inclusion of supportive living residents who, on average, live longer than the expected 18 months in long-term care facilities and assuming 33% of patients will be censored prior to any events, we find that 1232 patients would have 80% power (at a p of 0.05) to detect a difference between groups in the primary outcome of 27.6%. Although smaller differences would still be clinically meaningful, this difference is less than the 55% relative reduction in total mortality claimed in the MAPEC trial that we are trying to reproduce, and it is a very conservative minimum estimate for the actual power that the study will have. Additional power, while not directly calculable, will come in 2 ways: 1) These calculations assume no meaningful covariates and we have several covariates that are likely to be predictive of each outcome – in particular the resident's

level of care designation, and 2) we will continue to seek new facilities to partner with over the course of the trial – which should increase the number of residents available.

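### Residents with no post-randomisation MDS report are scored on their pre-randomisation report, which is expected to dilute nine secondary safety comparisons if missingness is similar in both arms

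*Combined protocol and SAP*

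**What the plan says.** The SAP's footnote to the safety outcomes defines the nine MDS-based outcomes: falls, urinary incontinence, skin ulceration and the six cognitive or behavioural measures. "Each are binary outcomes as recorded by usual care nurses in the Quarterly RAI-MDS report in the 3- to 6-month window post-randomization". It also limits them by level of care: "Safety outcomes 2 – 10 will only be examined in LTC residents". Safety outcome 1, non-vertebral fracture, is not MDS-based.

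The paragraph on missing MDS data, under the intention-to-treat assumptions, selects the report as follows: "we will use the post-randomization MDS nursing report closest to day 135 (tie going to the later date". It does not repeat the 3- to 6-month window. The fallback comes next: "If there are no such post-randomization reports we will use the report immediately preceding randomization". A participant is dropped only if no report of any kind exists, "which should not occur as a baseline MDS report is a routine part of every admission". In effect almost nobody is treated as missing.

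The protocol's outcome list takes the first assessment in the 3- to 6-month window and has no such fallback. The SAP's sensitivity analyses do not address missing MDS reports.

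**The concern.** A report completed before randomisation cannot be changed by allocation. Used as an outcome, it adds residents whose expected between-arm difference is zero, and the analysis counts them as observed. For the cognitive-deterioration item, which looks back 90 days, the whole comparison period then precedes the intervention.

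The SAP moves each facility's effective randomisation date to the day the allocation list was acted on. One stated reason is that "we are placing an equal emphasis on detecting harm"; another is that long delays make the arms look alike and hide harm. The missing-data rule brings the same kind of dilution back into the harm outcomes. Bias toward no difference may be called conservative for an efficacy claim. For a safety claim it favours a finding of no harm.

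**Working it through.** **The plan's own figure.** The documents give no rate of missing MDS reports and no power for the safety outcomes. Their one reproducible design figure is 301 events. For a hazard ratio of 1 − 0.276 = 0.724, two-sided 0.05, 80% power and 1:1 allocation, 4(1.960 + 0.842)² / (ln 0.724)² = 301. It concerns the primary outcome and this rule does not touch it.

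**Inputs.** Protocol section D gives a median lifespan of 18 months for new admissions and a "9 month median lifespan of those already resident at the time of the study". The 3-year median used there for power allows for supportive living residents, who are outside these nine analyses. Exponential survival, and a first eligible report spread evenly over its interval, are assumptions.

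**Step 1: share without a report, from deaths alone.** m = 1 − average of exp(−t·ln 2 / median) over the report interval. If only a report in the window counts (SAP outcome footnote), t runs over months 3 to 6. If any post-randomisation report counts (missing-data paragraph read alone), t runs over months 0 to 3.

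**Step 2: effect on the estimate.** Let p be an arm's risk among residents with a report, and b the baseline prevalence among those without one. The analysed risk is (1 − m)p + mb. With m and b equal in both arms, the risk difference is multiplied by (1 − m). If b also equals the control risk, a true risk ratio of 1.50 is seen as 1.50 − 0.50m.

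**Step 3: effect on the test.** Carrying baseline forward gives z proportional to (1 − m)√N. Analysing observed reports gives z proportional to √((1 − m)N). The ratio is √(1 − m), ignoring small changes in variance.

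| Reports that count | Median | m | RR seen (true 1.50) | z lower by |
|---|---|---|---|---|
| Any post-randomisation | 18 months | 0.056 | 1.47 | 2.8% |
| Any post-randomisation | 9 months | 0.107 | 1.45 | 5.5% |
| 3–6 months only | 18 months | 0.159 | 1.42 | 8.3% |
| 3–6 months only | 9 months | 0.291 | 1.35 | 15.8% |

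**Step 4: power, for illustration.** Assume 400 long-term care residents per arm, control risk and baseline prevalence both 20%, and a true risk ratio of 1.50. Power is 90.6% with no missing reports.

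| m | Baseline carried forward | Observed reports only |
|---|---|---|
| 11% | 83.5% | 87.0% |
| 16% | 79.3% | 85.1% |
| 29% | 65.8% | 78.7% |

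Filling these residents in therefore costs more power than leaving them out.

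**Step 5: unequal missingness.** Take 15% missing at bedtime and 25% in the morning arm, baseline prevalence 10% and control risk 20%. With no true effect, the risk ratio seen is (0.85 × 0.20 + 0.15 × 0.10) / (0.75 × 0.20 + 0.25 × 0.10) = 0.185 / 0.175 = 1.06. A true 1.25 is seen as 0.2275 / 0.175 = 1.30. With the missing shares reversed, the figures are 0.95 and 1.15. The direction is not fixed when missingness differs this much.

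**The case against.** The strongest reply is that the reach is limited. These are secondary outcomes in one level of care. A resident harmed early who dies still counts in the primary outcome and in all-cause mortality. Unplanned hospitalisation and fracture have their own analyses. This stands, and it lowers the severity.

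The size is also uncertain. The missing-data paragraph, read alone, lets any post-randomisation report count, which gives the smaller figures. The SAP excludes residents who were in hospital on the implementation date, so early mortality may be lower than the protocol's medians imply. Moves could raise m, but the SAP censors movers without saying how that applies to a binary MDS outcome. The protocol says MDS is recorded quarterly in all institutions, so movers may still have reports. All of this stands: m is an assumption.

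An observed-report analysis has its own weakness: it conditions on survival to assessment, which treatment might affect. That also stands, and calls for a sensitivity analysis that counts death. It does not justify a pre-randomisation value as the outcome. Intention-to-treat requires analysis by allocation, and the rule adds nothing to that.

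A reader might infer three stronger things. One is that every one of these comparisons must be pulled toward the null; Step 5 shows that this needs similar missingness by arm. Another is that the SAP deliberately scores the dead at baseline; the rule never mentions death, and the defect is that nothing exempts it. The third is that the 2024 amendment's statement that no harm was shown rests on this rule; the log does not say which outcomes support it.

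**Conclusion.** The rule should be changed, though it does not threaten the primary result. As written, it puts pre-randomisation values into nine safety comparisons at full sample size, and no other part of the plan corrects for this. Dilution is the expected effect when the share without a report and the baseline risk of those residents are similar by arm. With deaths as the only cause and the protocol's medians, the z-statistic loses about 3% to 5.5% on the wider reading of which reports count and 8% to 16% on the narrower. The mechanism is certain. The size depends on exponential survival, the timing of reports and a baseline prevalence equal to control prevalence, none of which the documents supply.

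**What to change.** 1. Reconcile the report window between the safety-outcome footnote and the missing-data paragraph, and state how death and moves between facilities are handled for outcomes 2 to 10.
2. Make the main analysis of these outcomes use residents with an eligible post-randomisation report, adjusted for the resident's own baseline MDS value. Table 2 now adjusts for facility-level prior rates only. Put the new covariate at the head of each list so that the limit on covariates per outcome does not drop it.
3. Report by arm how many residents had no report, and why (death, move, other).
4. Add a sensitivity analysis of outcome present or died before assessment. If imputation is used, restrict it to residents alive at the assessment time.
5. Keep the present rule only as a labelled sensitivity analysis, run with the covariates already listed.

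The cost is a rewritten SAP paragraph, an edit to Table 2 and modest programming, with no new data. The main analysis becomes conditional on survival to assessment, which item 4 addresses, although deaths may dominate that composite. The SAP predates the interim analysis, and the amendment log shows that results were known by October 2024. The change should therefore be dated and described as made after that point, with the prespecified analysis still reported.
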